After obtaining informed consent, all eligible patients (*n* = 150) will be randomly divided into three groups, according to the clinical approach used during endodontic therapy: in group 1—root canal treatment in a single visit (RCT-SV): endodontic treatment in a single visit using chemomechanical preparation (rotary NiTi instruments, 5.25% NaOCl, 17% ethylene diamine tetraacetic acid (EDTA)) and passive ultrasonic irrigation (PUI), followed by obturation (gutta-percha and epoxy resin-based sealer) and final restoration (composite resin); group 2—root canal treatment in two visits with intracanal dressing (RCT-TVWD): endodontic treatment in two visits using chemomechanical preparation (rotary NiTi instruments, 5.25% NaOCl, 17% EDTA) and PUI, followed by intracanal dressing [Ca(OH)2 powder paste mixed with camphorated paramonochlorophenol (CPMC) and glycerin in 3:1:1 proportion] and temporary restoration (glass ionomer cement (GIC)) for 7 days. After 7 days, an identical chemomechanical preparation on visit 2 was performed, followed by obturation (gutta-percha and epoxy resin-based sealer) and final restoration (composite resin); and group 3—root canal treatment in two visits without intracanal dressing (RCT-TVWOD): endodontic treatment in two visits using chemomechanical preparation (rotary NiTi instruments, 5.25% NaOCl, 17% EDTA) and PUI, followed by temporary restoration with composite resin (in order to avoid contamination of the root canal system) for 7 days, without intracanal dressing. After 7 days, an identical chemomechanical preparation on visit 2 was performed, followed by obturation (gutta-percha and epoxy resin-based sealer) and final restoration (composite resin). The follow-up period will be 24 months, with clinical data collected soon after endodontic therapy. Patients’ preference in choosing the number of clinical visits and the satisfaction rate after completion of treatment will be noted. Patients’ postoperative pain levels will also be recorded in periods of 24, 48, and 72 h and 7 days. Subsequently, clinical findings and long-term follow-up evaluations, with periradicular repair, will be performed by IOPAR at 6 and 12 months and CBCT at 24 months of follow-up.

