## Methods: participants, interventions, and outcomes

### Study setting {9}

The study will be conducted in the private offices of two of the co-investigators involved in the study ([name] and [name]), located in the cities of Itabuna (Bahia) and Goiânia (Goiás), Brazil, respectively. All investigators and examiners are specialists in Endodontics with more than 10 years of clinical experience. They will participate in this randomized clinical trial after receiving adequate training to obtain a comprehensive view of the principles and strategy of the 3 clinical approaches that will be used. A total of 150 adult patients, aged between 18 and 60 years old, who voluntarily seek endodontic treatment in the Brazilian Unified Health System in the cities of Itabuna, in the State of Bahia, and in Goiânia, in the State of Goiás, Brazil. After an assessment of eligibility and informed consent, patients will be randomly assigned to one of 3 clinical study groups. Patients who agree to participate in this study will sign an informed consent form.

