## Sample size and statistical methods

### Sample size details

The required sample size was calculated based on the preliminary outcome parameter of success, in a sequential approach, with each clinical case (tooth) serving as the statistical unit. Clinical studies that allow us to estimate, by means of CBCT, the repair index (complete absence of periapical radiolucency), therefore the success, after endodontic treatment of teeth with apical periodontitis and periradicular lesion, state that it is necessary to have a follow-up of at least 2 years to determine the success or failure of the treatment [22, 23]. After the first year of follow-up, post-endodontic treatment, it is still possible to observe the presence of periapical radiolucency in 52 to 84% of cases [1, 24, 25]. The sample will consist of 210 mandibular molars (first or second molars), based on statistical sample calculation, considering a power of 80%, an alpha value of 0.05, and an effect size of 20%. All patient characteristics at the beginning of treatment, such as age, gender, lesion size, among others, will be considered in the statistical analysis, in order to confirm the randomization of groups and the possible confounding effect of these characteristics.

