## Assignment of interventions: allocation

### Sequence generation {16a}

Assignments will be prepared by the statistician author of this study ([name]) prior to the trial start. A total of 150 patients (210 teeth) will be recruited and divided into 3 groups at a ratio of 1:1:1, namely, the RCT in a single visit, RCT in two visits with intracanal dressing, and RCT in two visits without intracanal dressing.

Randomization and allocation will be performed before all the clinical procedures.

First, a list of numbers from 1 to 210 will be created, each of the number represents one participant, then the list of numbers was assigned randomly following simple randomization procedures, by using Excel 2019 (Microsoft, Redmond, WA, USA) into three groups of 50 participants (70 teeth) each. Eventually, two columns in the spreadsheet are used, the first column contains the number of the participant (teeth) and the second contains the group to which the participant (teeth) is allocated, determined solely by the software.

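### The randomisation list has 210 numbers, each called a participant, for 150 patients with 210 teeth, so the unit of randomisation is undefined and a patient's teeth may fall in different arms

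*Protocol article*

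**What the plan says.** The protocol article uses two units without choosing between them.

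- Sequence generation {16a} gives the totals: "A total of 150 patients (210 teeth) will be recruited and divided into 3 groups at a ratio of 1:1:1". It then describes the list: "First, a list of numbers from 1 to 210 will be created, each of the number represents one participant". The numbers are "assigned randomly following simple randomization procedures, by using Excel 2019", and the result is a division "into three groups of 50 participants (70 teeth) each". In the spreadsheet, "the first column contains the number of the participant (teeth) and the second contains the group to which the participant (teeth) is allocated".
- Trial design {8} randomises patients: "all eligible patients (*n* = 150) will be randomly divided into three groups". Study setting {9} agrees: "patients will be randomly assigned to one of 3 clinical study groups".
- Intervention description {11a} describes the teeth as being randomly divided among the three groups.
- Sample size details works by tooth, "with each clinical case (tooth) serving as the statistical unit". Sample size {14} admits adults with one or more eligible teeth and mentions an adjustment for correlation between teeth of the same person.
- Concealment mechanism {16b} places each number, with its group, in its own envelope.
- Secondary outcome analysis compares pain and satisfaction between groups by the Kruskal-Wallis test, and visit preference by the chi-square test. All three come from patient questionnaires.

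No section says that all teeth of a patient take the same arm, or how a patient with teeth in two arms enters the patient-reported comparisons.

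**The concern.** A number cannot stand for both a participant and a tooth when some patients contribute several teeth. Each reading leads to a different problem.

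If a number is a tooth, a patient with two eligible molars uses two independently allocated envelopes. That patient may have one tooth treated in a single visit and another in two visits, which does not fit the parallel-group design stated in Trial design {8}. The Kruskal-Wallis and chi-square tests assume that each person contributes to one group only. A split patient either contributes to two or three groups or has no group, and the article does not say which.

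If a number is a patient, the list has 60 entries more than there are patients. Balance over 210 entries then does not secure balance over the 150 that are used.

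What is at stake is whether the allocation can be reproduced from the text, and whether the three patient-reported comparisons are valid. No analysis can afterwards give a split patient one randomised arm for an outcome that is recorded once per person.

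**Working it through.** **Inputs from the document.** 150 patients, 210 teeth, three arms, 50 participants and 70 teeth per arm (Sequence generation {16a}); one or more teeth per patient (Sample size {14}); lower first and second molars eligible (Inclusion criteria), hence at most four teeth per patient.

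**Assumptions.** The distribution of teeth per patient and the intra-patient correlation (ICC) are not given, so ranges are shown.

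**Step 1: the article's own totals.** 3 × 50 = 150 participants and 3 × 70 = 210 teeth. The totals agree with each other. The list length of 210 matches the teeth, while the unit named for each number is the participant. The excess is 210 − 150 = 60.

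**Step 2: numbers used for teeth.** Take a list with exactly 70 entries per arm in random order. For a patient with two teeth, the second tooth falls in another arm with probability 140/209 = 0.67. For a patient with k teeth, P(split) = 1 − 3 × C(70,k)/C(210,k).

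| Where the 60 extra teeth come from | Expected split patients | Share of 150 |
|---|---|---|
| 60 patients with two teeth | 60 × 140/209 = 40.2 | 27% |
| 30 patients with three teeth | 26.8 | 18% |
| 20 patients with four teeth | 19.3 | 13% |

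In 20,000 simulated shuffles, the two-tooth case gave a mean of 40 split patients (95% range 33 to 47) and the four-tooth case a mean of 19 (17 to 20). Each arm held on average about 63 and 59 distinct patients respectively. Exactly 50 distinct patients in every arm never occurred.

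**Step 3: numbers used for patients.** If 150 of 210 shuffled entries are used, each arm receives 50 on average, with SD = √(150 × 1/3 × 2/3 × 60/209) = 3.1. The probability of exactly 50/50/50 is C(70,50)³/C(210,150) = 0.019. The stated arm sizes are therefore expected only approximately.

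**Step 4: cost of patient-level randomisation for the tooth-level outcome.** The design effect is 1 + (m* − 1) × ICC, where m* is the sum of squared teeth per patient divided by total teeth.

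- 60 patients with two teeth: m* = (60 × 4 + 90 × 1)/210 = 1.571. For an assumed ICC of 0.1 to 0.5 the design effect is 1.06 to 1.29, or 199 to 163 effective teeth.
- 20 patients with four teeth: m* = (20 × 16 + 130 × 1)/210 = 2.143. The design effect is 1.11 to 1.57, or 188 to 134 effective teeth.

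**The case against.** The phrase about 50 participants (70 teeth) per arm, together with the parallel-group label, suggests that whole patients were meant to be allocated. That is a fair reading of the intention. It does not cure the defect, because a 210-number list without a rule linking the teeth of a patient does not carry it out.

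Pain and satisfaction can also be tied to a treatment episode. Plans for assessment and collection of outcomes {18a} times both from completion of a root canal treatment, so unless two teeth are treated together each answer has a tooth and an arm. This stands. For these two outcomes the remaining problem is that one person contributes dependent answers to different groups, with possible carry-over. Preference is asked under hypothetical conditions and is a property of the person, so for split patients it has no single arm.

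Three stronger inferences are tempting, and the document supports none of them.

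- A reader might infer that simple randomisation cannot give 70 teeth per arm. The list is prepared before the trial and divided into groups of stated size, which is compatible with shuffling a fixed list. That would give exactly 70 per arm. At most the label is loose.
- A reader might infer that the healing comparison is invalid. Healing is assessed by tooth, and randomising teeth does not in itself bias it. Sample size {14} acknowledges correlation within a patient.
- A reader might infer that running the trial in two cities without stratification is an error. Unstratified allocation is valid, and nothing in the article promises otherwise.

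**Conclusion.** The concern holds. Sequence generation {16a} contradicts itself on what a randomisation number is, the other sections do not settle it, and nothing keeps a patient's teeth in one arm.

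The size depends on the reading. With tooth numbers, about 19 to 40 of 150 patients (13% to 27%) are expected to have teeth in different arms. The upper end assumes 60 patients with two teeth and the lower end 20 patients with four. The effect is on the independence of the pain, satisfaction and preference comparisons, and on the arm to which preference belongs, for those patients only. With patient numbers, the list is 60 too long and does not guarantee 50 per arm.

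The article does not show that any patient has in fact been split. It shows that the stated procedure allows it. Because the unit of randomisation decides who belongs to which arm, it must be corrected rather than left to interpretation.

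**What to change.** **For patients not yet randomised.** Make the patient the unit. Use a 150-number list with a fixed 50 per arm, and state that all eligible teeth of a patient follow that patient's arm. Bring Trial design {8}, Study setting {9}, Intervention description {11a}, Sample size details and Sequence generation {16a} into agreement. Analyse healing by tooth with clustering by patient, and pain, satisfaction and preference once per patient.

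**For patients already randomised tooth by tooth.** Keep teeth as allocated. Do not exclude split patients from the main comparisons, since that would conflict with the intention-to-treat plan in section {20c}. Attribute pain and satisfaction to the arm of the first-randomised (index) tooth, or use a model clustered by patient, and add a sensitivity analysis without split patients. For preference, state which convention is used, because no allocation defines its arm. Report how many patients were split.

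**Cost.** New envelopes and revised wording, slightly unequal numbers of teeth per arm, and the design effect shown in step 4 (about 1.06 to 1.29 with 60 two-tooth patients and an assumed ICC of 0.1 to 0.5; more if fewer patients carry more teeth). Trial status gives August 2021 as the start of recruitment and December 2024 as the estimated end. If that end includes the 24-month follow-up, the last treatment falls near December 2022. A new list may then reach few patients, and the rules for those already allocated become the main part of the fix.

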### Eligibility criteria {10}

#### Inclusion criteria

To enroll in the study, subjects must (1) be diagnosed with apical periodontitis in lower molar teeth (first or second molars), the periradicular lesion with a diameter between 1 and 5mm analyzed through the real tomographic scale of 1:1; (2) be asymptomatic; (3) spontaneously agree and sign the informed consent form; (4) have an absence of any chronic systemic disease; and (5) be not taking antibiotics and anti-inflammatory drugs.

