#### Baseline analysis

The three groups will be similar in terms of disease type and periapical lesion size.

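### One unstratified simple-randomisation list serves two office sites, yet the protocol fixes 70 teeth per group and asserts similar lesion size, neither of which that method secures

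*Protocol article*

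**What the plan says.** All references are to the protocol article.

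- **Sequence generation {16a}** describes a single list: "First, a list of numbers from 1 to 210 will be created, each of the number represents one participant". It is assigned "following simple randomization procedures, by using Excel 2019", "into three groups of 50 participants (70 teeth) each", and "the second contains the group to which the participant (teeth) is allocated, determined solely by the software". The ratio is 1:1:1 for 150 patients and 210 teeth. No stratum, block, minimisation factor or site-specific list is described.
- **Baseline analysis**, under Statistical methods, states: "The three groups will be similar in terms of disease type and periapical lesion size".
- **Inclusion criteria** admit "the periradicular lesion with a diameter between 1 and 5mm", measured on the tomographic scale, so lesion diameter is known before allocation.
- **Study setting {9}** says: "The study will be conducted in the private offices of two of the co-investigators involved in the study". The offices are in Itabuna and Goiânia. Exclusion criteria says that the examiners who complete the diagnosis also perform the treatment, and Outcomes {12} refers to two examiners.
- **Sample size details** says that baseline characteristics, lesion size among them, will be taken into account in the analysis, to confirm the randomisation and look at possible confounding. Site and operator are not named.
- **Main outcome analysis** compares success rates by the Kruskal-Wallis test. **Methods for additional analyses {20b}** plans none.

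**The concern.** Two statements do not follow from the allocation method described.

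1. *Group sizes.* Simple randomisation assigns each unit independently, so arm sizes vary at random. A fixed 70 teeth per group needs a restricted list. Either the name of the method or the group sizes are misdescribed.
2. *Baseline similarity.* The protocol states as a fact something the method delivers only on average. Lesion diameter may range five-fold (1 to 5 mm), and the protocol itself treats lesion size as a possible confounder. Site has the same exposure. If each office has one operator, which is an inference from Study setting, Exclusion criteria and Outcomes, then site and operator are the same factor.

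At stake is the reading of the primary result. If an arm happens to receive more large lesions or more of one operator's cases, its success rate may shift for that reason, and the stated test has no term through which to allow for it.

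**Working it through.** **Inputs from the protocol:** 210 teeth, three groups, 70 teeth per group, 150 patients, two sites, lesion diameter 1 to 5 mm, effect size 20%.

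**Assumptions (not in the protocol):** half the teeth have larger lesions; teeth are independent; site shares lie between 50:50 and 70:30.

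**1. Do the stated group sizes follow from simple randomisation?**

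- P(exactly 70/70/70) = 210! / (70!)³ / 3²¹⁰ = 0.0039, or 0.39%.
- SD of one arm's size = √(210 × 1/3 × 2/3) = √46.67 = 6.8 teeth. By simulation, the central 95% of one arm runs from 57 to 84 teeth.
- For patients, P(exactly 50/50/50) = 150! / (50!)³ / 3¹⁵⁰ = 0.55%.

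The equal groups therefore imply a fixed-size list, which the section does not call by that name.

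**2. How much lesion imbalance does a fixed-size, unstratified list leave?** Take 105 larger and 105 smaller lesions allotted at random to three arms of 70. The numbers of larger lesions in the arms, (a, b, c) with a + b + c = 105, have probability C(70,a) × C(70,b) × C(70,c) / C(210,105). Summing over all splits, with gaps expressed as a share of 70:

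| Gap in share of larger lesions | Largest of three pairs | One named pair |
|---|---|---|
| Mean | 10.1 points | 6.7 points |
| 10 points or more (7 teeth or more) | 51% | 27% |
| 15 points or more (11 teeth or more) | 18% | 7.6% |

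On a continuous scale, the largest standardised difference in mean lesion size between two of the three arms is at least 0.2 SD in 46% of simulated lists and at least 0.3 SD in 18%.

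**3. Site.** With equal enrolment the arithmetic is the same as in step 2. By simulation, over site shares from 70:30 to 50:50, the largest between-arm gap in site share is at least 10 points in 45% to 52% of lists and at least 15 points in 13% to 18%. If the 150 patients are the units, these become 61% to 66% and 24% to 30%.

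**4. What stratification would achieve.** With permuted blocks of 6 within site and lesion category (210 teeth), the median largest gap in site share is 1.4 points, against 9 to 10 points for the single list. Gaps of 10 points or more did not occur in 20,000 runs at either site share.

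**5. Effect on an arm contrast.** Shift = gap in the share of larger lesions × difference in success between smaller and larger lesions. The protocol gives no figure for the second term; 20 to 30 points is assumed.

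- Mean gap of a named pair: 0.067 × (0.20 to 0.30) = 1.3 to 2.0 points.
- Gap of 15 points: 0.15 × (0.20 to 0.30) = 3.0 to 4.5 points.

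For scale, the standard error of a difference between two arms of 70 is √(2p(1−p)/70), which is 8.3 points at p = 0.60 and 6.8 points at p = 0.80 (success rates assumed).

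**The case against.** **Unstratified randomisation is valid.** This stands. Expected imbalance is zero, and the test's error rate already allows for chance imbalance. A reader might infer that the trial is biased or its comparison invalid; the documents do not support that. The shifts in step 5 are what a particular allocation may produce, not a systematic error.

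**Lesion size is not ignored.** A reader might infer from the Kruskal-Wallis test alone that baseline lesion size plays no part in the analysis. Sample size details says otherwise, and how it is done may be left to an analysis plan that is not shown. That answers part of the concern for lesion size. It does not cover site or operator, and the primary test that is named cannot carry the adjustment.

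**The largest of three gaps is the least favourable summary.** This also stands, so the named-pair figures are given beside it. Typical shifts are small against the standard error and against the 20% effect size. That full repair depends on lesion size is plausible, but the protocol speaks only of possible confounding.

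**The method's name may be loose usage.** The section can be read as a random split into fixed sizes. On that reading the arm-size point is one of terminology, but the description still needs correcting, and nothing changes for lesion size or site.

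**Envelopes.** A reader might infer that one numbered series cannot be used in order in two cities. Concealment mechanism {16b} does not say how envelopes are distributed. Number ranges could be given to each office, and Recruitment {15} describes close coordination between them. The inference is not supported.

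**Conclusion.** The concern holds in a limited form. The allocation section combines a method with group sizes that it yields exactly in only 0.39% of realisations, and the baseline section asserts a similarity in lesion size that the method secures only in expectation. Site, which is probably also operator, is addressed neither in the allocation nor among the characteristics named for the analysis.

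Under the 50% assumption, an 18% chance that some pair of arms differs by 15 points or more in the share of larger lesions (7.6% for a named pair) is enough to make an unconditional promise of similarity unsafe. It is not evidence of systematic bias, and it does not invalidate the randomisation. The imbalance figures rest on the assumed lesion split and site shares and on independent teeth; teeth clustered within patients would make imbalance more likely. The effect on an arm contrast rests also on an assumed prognostic difference.

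Stratifying alone would not settle the matter. Recruiting began in August 2021 and the estimated end is December 2024 (Trial status). If that end date includes the 24-month follow-up, enrolment would close around December 2022, so few allocations may remain to be changed.

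**What to change.** 1. **Sequence generation {16a}:** restate the method so that it matches the fixed group sizes. Keep all allocations already made. For those not yet made, use permuted blocks of varying, concealed size, with a separate list and envelope series per site, stratified by lesion-size category on the screening CBCT (for example 1 to <3 mm and 3 to 5 mm, giving four strata). State which lesion sets the stratum when a patient contributes more than one tooth.
2. **Main outcome analysis:** carry out the intention in Sample size details by adjusting the primary success comparison for site and baseline lesion diameter. Logistic regression reported as risk differences, allowing for teeth clustered within patients, would serve. This covers every allocation, including those already made, and keeps the gain in precision that stratification with an unadjusted test would largely forgo.
3. **Baseline analysis:** replace the assertion with a plan to describe baseline lesion size by group.

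**Cost:** new lists and envelopes for the remaining allocations, a protocol amendment with ethics approval under item {25}, and slightly more analysis work. No extra patients or procedures are needed, since lesion diameter is already measured for eligibility. If no allocations remain, only the corrected description of the method in item 1, together with items 2 and 3, applies.
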